### Study design

This is a phase-4 study of an approved drug, with the aim to delineate additional information for its optimal usage and efficacy. It is designed as a cluster randomised, open-label trial with two study arms, with the ultimate aim of comparing the endpoint results in the intervention versus control arm. A community cluster randomised trial in different settings in Ghana will evaluate the impact and cost-effectiveness of twice-yearly and yearly MDA. The primary outcome is the prevalence of LF. This outcome is selected because it is the prevalence of LF that determines the level of on-going transmission (both parasitological and entomological) and the need to implement Transmission Assessment Surveys and stop MDA [19]. Allocation to study group will be by villages, identified through programme reports, and by disease-control officers in the study districts. The mf prevalence in all communities will be re-evaluated, based on nucleopore filtration of 1 ml of night-blood collected from study participants, prior to assignment to study groups.

The two study groups are:Control group: annual MDA. Clusters (with members aged 5 years and above) will receive 400 μg/kg IVM + 400 mg ALB from trained community drug distributors (CDDs), as part of the ongoing national MDA programmeExpanded frequency group: annual MDA with 400 μg/kg IVM + 400 mg ALB, followed by an additional MDA 6 months later. The drugs will be provided by the national programme and administered by the CDDs, following the structures of the National MDA programme

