### Sample size calculation

The sample size was calculated based on the null and alternative hypotheses, together with the type-I and type-II errors defined as follows:

Null hypothesis (H_0_): the additional dose of IVM is not more effective than the standard single dose per annum treatment (i.e. Treatment – Control = 0).

Alternative hypothesis (H_A_): the additional dose of IVM is more effective than the standard dose (i.e. Treatment − Control > 0).

The type-1 error rate (*α*), i.e. rejecting H_0_ when it is true, is set at 0.05, with a two-sided test. To control for type-II error (*β*), the probability of rejecting H_0_ when it is false is set at 0.80, taking into consideration budget allocation.

The hotspot districts have been receiving an annual single dose of IVM for the past 15 years with the prevalence rates ranging between 1% and 18.2%. Therefore, it is assumed that the new intervention would have an effect, expected to be larger than the effect of the standard control approach, with an effect size of 0.4. Based on these assumptions, the sample size was calculated using the Optimal Design software [34]. Thus, for 0.80 power the study requires a cluster size of 58.

With an expected non-response and a loss to follow-up of 37% (determined from previous unpublished studies), the sample size per cluster has been determined to be 80. With 18 clusters to be surveyed, a total of 1440 study participants, from the two study districts, will be expected to take part in this trial.

Study participants will not be paid as part of the survey. However, in order to mitigate the high dropout rates during follow-ups, participants will be compensated for the time lost for working during the days they are participating in survey activities, with an amount of 7 Cedis (equivalent to US$1.61). They will also be contacted at 14 days and 7 days prior to follow-up, in order to ensure their availability. Even though there is always the possibility of emergencies and other social responsibilities that may result in their unavailability, efforts will be made to reach them.

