### Cluster randomisation

Randomisation will be stratified by the prevalence of LF (as determined in the baseline surveys). The randomisation sequence generation will be undertaken by an independent statistician using computerised random-number generation. Sealed envelopes containing cluster identification will be placed in pre-stratified ballot boxes, with community leaders invited to select envelopes from the boxes and directed to put the selected envelope in a box labelled A or B (corresponding to the two study groups, each with nine clusters) according to the pre-generated randomisation sequence for that stratum. With an average household size of six and the frequency of under 5 years being 14.3%, 45 households will be randomly selected in each cluster and five eligible household members recruited into the cross-sectional surveys. Owing to the nature of the interventions, participants will not be blinded to their group randomisation. However, the identity of the study groups will remain hidden until the completion of community sensitisation and randomisation in order to eliminate participation bias. Further, the laboratory technicians conducting the parasitological examinations and the statistician responsible for analysis will be blinded to the group assignment. The blinding to the laboratory technicians and statistician will be done using sample/study participant identification codes for samples and results which will not be linked to the study groups.

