The summary statistic for each parasitological endpoint will be estimated, and compared using paired Student’s *t* tests. Changes in rate of infection will be expressed as percentage differences from the pre-treatment rates. The significance in differences in mosquito infection rates will be tested using the chi-square test. The significance of correlation between different indices will also be tested using the chi-square test. The significance of differences in monthly transmission potential before and after treatment will be tested with the non-parametric Mann-Whitney *U* test. Analysis of variance (ANOVA) will also be used in the intent-to-treat analysis for comparing the study groups. SPSS for WINDOWS 16 (SPSS Inc, Chicago, IL, USA) will be used for all statistical computations. The mf intensities will be adjusted for sampling time by multiplying the counts with a time-specific factor [38]. Geometric mean intensities (GMIs) of microfilaraemia and antigenaemia prevalence will be calculated [39].

Below is the statistical analysis strategy.

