#### Pre-post analysis

Since the emphasis is on the comparison of the intervention and control groups, each of the follow-up measurements will be analysed in relation to the baseline measurements of the outcome in a pre-post analysis. For instance, Y_i0_ = 1 to Y_i1_ = 0 in Eq. 1 would indicate a favourable effect of the intervention in group 2 while Y_i0_ = 1 to Y_i1_ = 1 would indicate no effect and Y_i0_ = 0 to Y_i1_ = 0 will be considered a preventive effect:1$$ \left\{\begin{array}{l}{Y}_{\mathrm{i}0}=1\to {Y}_{\mathrm{i}1}=0\hfill \\ {}{Y}_{\mathrm{i}0}=0\to {Y}_{\mathrm{i}1}=1\hfill \\ {}{Y}_{\mathrm{i}0}=0\to {Y}_{\mathrm{i}1}=0;\kern1em {Y}_{\mathrm{i}0}=1\to {Y}_{\mathrm{i}1}=1\hfill \end{array}\right., $$

where the baseline measurement of the outcome for the i^th^ participant is given by Y_i0_;

Y_i1_ denotes the measured outcome at the first follow-up; and 1, 0 indicate the presence or absence of LF infections, respectively.

Therefore, by subsetting on each of the possible scenarios of the baseline measurements (Eq. 2), the control and intervention groups could be compared using second-order transition models where separate logistic regression models will be fitted for each of the possible scenarios:2$$ \left[\begin{array}{ll}\upchi 00\hfill & \upchi 01\hfill \\ {}\upchi 10\hfill & \upchi 11\hfill \end{array}\right], $$

where χ_00_ is the probability that the follow-up measure of the outcome and Y_ij_, is 0 when the baseline measurement is also 0.

Results will be presented separately for every time point and then after the study, the overall effect of the intervention will be analysed, taking all time points into consideration. Further, after the first time point we would employ a generalised linear mixed model to account for the correlation between the repeated measurements per individual.

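### The models named for the primary comparison name no village effect although villages are randomised, so the nominal 5% test is anti-conservative by an amount that depends on an unstated ICC

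*Protocol article*

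**What the plan says.** The Study design section of the protocol article states: "It is designed as a cluster randomised, open-label trial with two study arms". It adds: "Allocation to study group will be by villages". The Sample size calculation section gives the scale ("With 18 clusters to be surveyed, a total of 1440 study participants"), and the Cluster randomisation section gives the split ("corresponding to the two study groups, each with nine clusters"), stratified by baseline prevalence.

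The primary hypothesis is tested in the Pre-post analysis section. Outcomes there are indexed by participant and coded 0 or 1. At each time point the arms are compared within baseline-status subsets: "separate logistic regression models will be fitted for each of the possible scenarios". For later time points the article says that "after the first time point we would employ a generalised linear mixed model to account for the correlation between the repeated measurements per individual". The correlation named is within person.

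The Data management and analysis section adds two further methods:
- "The summary statistic for each parasitological endpoint will be estimated, and compared using paired" Student's t tests.
- "Analysis of variance (ANOVA) will also be used in the intent-to-treat analysis for comparing the study groups".

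Neither sentence gives the level (village or person) at which the test is done.

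**The concern.** People in one village share vectors, transmission intensity, drug distributors and treatment history, so their outcomes are correlated. When whole villages are allocated, that shared variation goes into the difference between arms. A model that handles only repeated measurements on the same person leaves it out of the standard error. With nine villages per arm, an ordinary chance difference between villages could then be reported as an effect of twice-yearly treatment, with a p-value and confidence interval that look firmer than they are. The article expects to make firm recommendations from this comparison, so the validity of the primary test matters.

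This goes beyond detail that a condensed article leaves to an analysis plan. The article names its models and says which dependence the mixed model is there to handle, and the unit of randomisation is not part of it.

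**Working it through.** **Step 1. Does any section supply the missing term?** Four places mention clusters or could imply a village-level analysis.
- Data management and analysis restricts analyses to clusters with baseline and endpoint results. This says which villages enter, not how between-village variance is handled.
- The same section adjusts for the cluster mean at baseline, but only for continuous outcomes. A covariate is also not a variance term, and the primary outcome is binary.
- The t test and ANOVA sentences do not state a level of analysis.
- The Analysis strategy under Secondary outcomes recognises within-group clustering and uses generalised estimating equations. That analysis regresses measured covariates on infection to study transmission dynamics. It does not test the arms on the primary outcome.

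None of them puts the village into the primary test.

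**Step 2. The plan's own figure.** Inputs from Sample size calculation: J = 18 clusters, effect size d = 0.4, two-sided alpha 0.05, power 0.80, n = 58 per cluster. No ICC is printed, so 58 cannot be reproduced directly. Assume that d is standardised and use the usual cluster-randomised formula: noncentral F on 1 and J − 2 = 16 degrees of freedom, with

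λ = J·d² / {4·[ICC + (1 − ICC)/n]}.

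The required n is 13 at ICC 0, 31 at 0.05, 46 at 0.06 and 86 at 0.07. Solving for n = 58 gives ICC = 0.0647. Check: λ = 18 × 0.16 / {4 × [0.0647 + 0.9353/58]} = 8.91, power 0.800. On this reading the sample size allowed for village clustering that the named primary models do not carry.

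**Step 3. People per village at follow-up.** The plan expects 58 complete. If 37% of the 80 recruited are lost, 80 × 0.63 = 50.4 remain. So m is about 50 to 58.

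**Step 4. Type I error with no village term.** Design effect DE = 1 + (m − 1)·ICC. True two-sided error of a nominal 5% test = 2·[1 − Φ(1.96/√DE)].

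| ICC (assumed) | DE, m = 50 | Error | DE, m = 58 | Error |
|---|---|---|---|---|
| 0.005 | 1.25 | 7.9% | 1.29 | 8.4% |
| 0.01 | 1.49 | 10.8% | 1.57 | 11.8% |
| 0.02 | 1.98 | 16.4% | 2.14 | 18.0% |
| 0.028 | 2.39 | 20.5% | 2.62 | 22.6% |
| 0.065 | 4.17 | 33.7% | 4.69 | 36.5% |

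The 0.028 row spreads village prevalences uniformly over the stated range of 1% to 18.2%: variance 0.172²/12 = 0.002465, mean 0.096, ICC = 0.002465/(0.096 × 0.904) = 0.028.

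**Step 5. By baseline status.** The Background gives 4.6% microfilaria and 13% antigen prevalence in two local communities.
- Baseline-positive model: 4.6% of 50 is 2.3 people per village and 13% of 58 is 7.5, so about 2 to 8. Over ICC 0.01 to 0.065 the error is about 5% to 10%.
- Baseline-negative model, from 58 per village: 0.87 × 58 = 50.5 to 0.954 × 58 = 55.3 people. The error is 11% to 36% over the same ICCs.

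**Step 6. Simulation check.** Beta-binomial data were simulated under the null: nine versus nine villages of 58, prevalence 4.6%, 10% and 13%, 20,000 runs per scenario. The test ignoring villages rejected in 11.5-11.7% of trials at ICC 0.01, 17.6-18.5% at 0.02 and 30.7-32.2% at 0.05. A village-level t test on 16 degrees of freedom rejected in 3.8-5.2% over ICC 0 to 0.10. This confirms the formula. It says nothing about which ICC applies in these villages.

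**The case against.** The strongest reply is that the article is silent rather than wrong. It prints no regression equation and no random-effects structure, and a separate analysis plan could add a village term. The planners knew about clustering: they handle it in the secondary analysis, and the sample size appears to allow for it. It stands that the models name no village effect, which is weaker than saying they exclude one. It does not remove the point, because the article states what the mixed model is meant to account for and names within-person correlation only.

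Three stronger readings are tempting, and the text does not support them.
- A reader might infer that the trial is analysed as 1440 independent people. The mixed model handles within-person correlation, the logistic models are split by baseline status, and the plan expects 58 complete per village (18 × 58 = 1044).
- A reader might infer that the error rate is far above 5% in every model, or reaches 43%. The size depends on an ICC that is not stated, and 0.065 rests on reading 0.4 as standardised. The 43% figure needs 80 per village, the number before losses. The baseline-positive model is barely affected. Stratified randomisation and conditioning on baseline status may also lower the residual ICC.
- A reader might infer that the ANOVA is individual-level and that the paired t test compares arms. Neither is stated. An ANOVA on 18 village summaries would be a valid comparison, and the paired test sits next to a sentence on change from pre-treatment rates, so before-after use is a natural reading. What can be said is that the level and purpose are left open.

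**Conclusion.** The point holds. Villages are randomised, the models named for the primary comparison name no village effect, and nothing elsewhere brings the village into that test. Run as written, the test is anti-conservative at any positive ICC. The omission can be read directly from the text, but its size is conditional. At 50 to 58 people per village, type I error is about 11-12% at ICC 0.01, 16-18% at 0.02, and 34-37% at the back-solved 0.065. These figures assume equal village sizes, a normal reference distribution, and no reduction in ICC from stratification or baseline conditioning. They apply to the baseline-negative model (with slightly smaller numbers) and the overall comparison, not to the baseline-positive model. Because this concerns the validity of the primary test and is easily corrected, it should be settled before the analysis.

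**What to change.** In Pre-post analysis, add a village random intercept to every primary model, with person nested within village where measurements repeat. Include the randomisation strata and use small-sample degrees of freedom: 18 − 2 = 16, fewer once strata or covariates enter. Alternatively, make the primary test a comparison of nine versus nine village-level prevalences.

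In Data management and analysis, state that any ANOVA comparing arms is done on village summaries. Restrict paired t tests to before-after change, since villages are stratified and not pair-matched across arms. State the ICC behind the sample size.

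The cost is wording only, with no change to sampling or fieldwork. Confidence intervals will be wider, but correct. At ICC 0.065, and with 0.4 taken as standardised, a village-level test has 80% power with 58 per village and about 79% with 50, so the design intent is essentially kept.

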### Secondary outcomes

A subsample of 80 individuals from the following clusters: low (1%), medium (2–4%) and high (>5%) LF prevalence; in each of the study groups will be followed longitudinally for 2.5 years in order to better understand the transmission dynamics of LF, and to estimate key parameters for mathematical modelling of transmission dynamics and treatment impact. Both the presence and intensity of *W. bancrofti* mf will be assessed at 3, 6, 9 and 12 months post treatment. Information on covariates that influence *W. bancrofti* mf transmission in humans, such as use of bed nets, will be measured at each of these endpoints.

#### Analysis strategy

Each of our study outcomes, i.e. prevalence and intensity of *W. bancrofti* mf, will be considered separately during the analysis. Loss to follow-up was taken into consideration during our sample size calculation. Therefore, regardless of the number of incomplete observations, we expect to end up with no less than 58 complete observations per community at the end of the study.

A panel of individual line plots for the study participants would be used in the assessment of within-person variability. Since the assumptions of likelihood are violated by the effect of within-group and within-subject clusters in longitudinal data, in assessing the transmission dynamics of LF infection, the measured covariates will be regressed separately on both the prevalence and the intensity of infections using a quasi-likelihood method, i.e. generalised estimating equations, which uses an association matrix instead of the diagonal matrix employed by the generalised linear models. As part of the model validation, the point-referenced residuals of the provisional models will be assessed for spatial autocorrelation. The results of this assessment would help to determine if unmeasured/unobserved factors in the study areas play relevant roles in the transmission dynamics of LF infections. Using classical geostatistical concepts, our final model would be adjusted for both the effects of the measured and unobserved factors.

For entomological endpoints, infection rates will be determined, using the polymerase chain reaction (PCR) [40] and LAMP [41] methods. The results will be analysed using the poolscreening software by Katholi and colleagues [42, 43].

The findings and data from this study will be used to develop a mechanistic model, which describes the variability in treatment responses in populations. This will be implemented into an already available and well-established transmission dynamic model for LF (LYMFASIM) [44, 45], which will then be used to systematically explore the consequence of twice-yearly treatment on the long-term impact of MDA and elimination prospects. LYMFASIM simulates the spread of *W. bancrofti* in a human community and the impact of control measures, with the advantage of accounting for a variety of parameters specific to the population of interest and output predictions [45, 46].

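### The GEE planned for the longitudinal mf outcomes rests on at most 18 villages and needs the village as cluster with a small-sample correction: run in the usual uncorrected way, an arm contrast has about 8% type I error

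*Protocol article*

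**What the plan says.** The Analysis strategy under Secondary outcomes treats mf prevalence and mf intensity separately. It notes that observations are dependent within groups and within subjects, and plans to regress the outcomes on the measured covariates "using a quasi-likelihood method, i.e. generalised estimating equations, which uses an association matrix instead of the diagonal matrix". Residuals of provisional models are then checked for spatial autocorrelation, and the final model is adjusted for unmeasured factors. The cluster unit, variance estimator and reference distribution are not named.

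The number of independent units is bounded by the design. Study population gives 18 clusters, and Cluster randomisation describes boxes A and B as "corresponding to the two study groups, each with nine clusters".

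How many villages enter the longitudinal work is less clear:
- Secondary outcomes takes 80 individuals from clusters of "low (1%), medium (2–4%) and high (>5%) LF prevalence; in each of the study groups", without a village count.
- Longitudinal surveys follows people positive for antigen and mf at baseline, also without a village count.
- Analysis strategy expects at least 58 complete observations per community.

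Data management and analysis restricts statistical testing to the comparison of the two treatment groups and says that secondary outcomes will be pre-specified for testing. The type I error "is set at 0.05, with a two-sided test".

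**The concern.** A standard GEE has one clustering unit, while the text recognises two levels. Because persons are nested in villages, taking the village as the unit covers both levels. The sandwich variance is then estimated from as many independent pieces as there are villages. With few villages it is too small on average, and its own variability is ignored when the statistic is referred to the normal distribution. Both faults make p-values too small and intervals too narrow. Taking the person as the unit leaves village correlation out of the variance, which matters most for an effect that varies only between villages, such as treatment arm.

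At stake is the reliability of intervals and tests for arm and covariate effects on mf prevalence and intensity in the longitudinal subsample.

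**Working it through.** **The plan's own figure.** The article states no error rate for the GEE. The nearest figure is the sample size: "for 0.80 power the study requires a cluster size of 58", "with an effect size of 0.4". No intraclass correlation (ICC) is given, so the 58 cannot be verified, but the ICC it implies can be found. For J = 18 villages, n persons each and standardised effect d = 0.4 (the scale is not stated; this is an assumption), power follows from a noncentral F on 1 and 16 df with λ = J·d² / {4[ρ + (1 − ρ)/n]}. At n = 58, power is 0.82 for ρ = 0.06, 0.80 for ρ = 0.065 and 0.78 for ρ = 0.07. The implied ICC is therefore about 0.065.

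**Arm contrast, village as cluster: closed form.** Take m villages per arm of equal size. The uncorrected sandwich divides the squared village residuals by m where an unbiased estimate divides by m − 1, so its variance is (m − 1)/m times the unbiased one. With a normal reference, the test rejects when |t| on 2m − 2 df exceeds 1.96·√[(m − 1)/m].

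| Villages | m | Effective cut-off | df | Type I error | Ratio to 5% |
|---|---|---|---|---|---|
| 18 | 9 | 1.96·√(8/9) = 1.848 | 16 | 8.3% | 1.7 |
| 12 | 6 | 1.96·√(5/6) = 1.789 | 10 | 10.4% | 2.1 |
| 6 | 3 | 1.96·√(2/3) = 1.600 | 4 | 18.5% | 3.7 |

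Eighteen is the stated total. Six would follow only from one village per prevalence level and arm (3 × 2), which the article does not state. Twelve is shown as an intermediate value.

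**Simulation check.** Logistic GEE with independence working correlation, no true effect and four visits per person. Assumed, not in the documents: village ICC 0.01 to 0.05, within-person correlation 0.5 and prevalence 5% to 35% (5% and 10% for the bed-net rows).

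| Effect tested | Cluster in GEE | 6 villages | 18 villages |
|---|---|---|---|
| Arm | Village, uncorrected | 17–25% | 8–12% |
| Arm | Village, m/(m − 1) correction and t on 2m − 2 df | about 4–6% | about 4–7% |
| Bed-net use (person level) | Village, uncorrected | 14–20% | 7–10% |

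**Person as the only cluster.**
- Arm contrast, 58 to 80 persons per village: 15–21% at ICC 0.01 and 39–50% at ICC 0.05.
- Arm contrast, 4 to 9 persons per village in 18 villages: 6–13%.
- Bed-net use: about 5–6% when net use does not vary by village, and 6–12% when it does.

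Person-only clustering is therefore worse than village clustering for an arm contrast in large villages at ICC 0.05. At ICC 0.01 with six villages the two are about equal, and for a person-level covariate the person-clustered error is generally the lower.

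**The case against.** The strongest reply is that the article names only GEE, which is a sound choice, and that the variance estimator and reference distribution are details usually left to an analysis plan. That stands: silence on them is no defect, and nothing in the text says that the variance will be uncorrected. The point is conditional. It concerns what the named method does in its usual form with a village count that the design itself caps at 18.

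A second reply is that the GEE serves covariate regression for transmission dynamics, and that other methods are named for comparing arms. This largely stands, and it is why the covariate figure of 7–10% is given beside the arm figure. It does not remove the arm contrast: Data management and analysis foresees testing secondary outcomes between arms, and GEE is the regression method named for these longitudinal outcomes.

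Third, the later spatial adjustment might absorb village-level dependence. It may absorb some, but it does not correct a sandwich variance or a normal reference for few clusters.

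A reader might infer more than the text supports:
- *Error of up to four times nominal.* This needs six villages, which is only one reading of the subsample description.
- *Village correlation is ignored.* The text mentions within-group as well as within-subject clustering, so a person-only GEE would go against it.
- *The transmission model inherits wrong p-values.* The article says that findings and data will inform the model, not that GEE tests or intervals enter it.

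**Conclusion.** The point holds in a limited form. At the stated 18 villages, a village-clustered GEE with an uncorrected sandwich and normal reference gives about 8% type I error for an arm contrast and about 7–10% for a person-level covariate. The arm figure would be about 18% if only six villages were used. The closed form assumes equal village sizes and no covariates. The simulated figures rest on the assumed ICC and within-person correlation, were obtained for a binary outcome, and were not run for intensity. Person-only clustering could be worse for the arm contrast, but by how much depends on figures that the article does not give. The primary comparison is not affected, so this is a modest but worthwhile correction to the secondary analysis.

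**What to change.** In Analysis strategy, state that the village is the GEE cluster. Specify a bias-corrected sandwich variance (for example Mancl-DeRouen or Kauermann-Carroll) with a t reference and small-sample, Satterthwaite-type degrees of freedom. Villages minus parameters is not a safe rule for the degrees of freedom: with six villages, fitting arm, prevalence level, time and covariates can exhaust it. State how many villages the longitudinal subsample covers.

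If it covers only about six, compare arms by a t test on village summaries and report covariate effects descriptively. A permutation test should not be used there. With three villages per arm there are 20 allocations, so the smallest two-sided p-value is 2/20 = 0.10. Permuting within prevalence level leaves 8 allocations and a minimum of 2/8 = 0.25.

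The change is to analysis wording, plus a check that the named package (SPSS 16, for all computations) offers the correction. The price is width. For the balanced arm contrast with an m/(m − 1) correction, intervals widen by a factor of 2.120·√(9/8)/1.96 = 1.15 at 18 villages and 2.776·√(3/2)/1.96 = 1.73 at six. Village summaries also cannot estimate person-level covariate effects, which is why those would be descriptive in the six-village case.
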